## Anticipated results

We expect this project to provide insight into the effectiveness of user-generated content in reducing excessive consumption. We hope the project will shed light on specific aspects of user-generated content that help reduce excessive consumption and increase well-being. We predict to find data supporting our hypotheses and we therefore anticipate reduced excessive consumption within the intervention groups, as well as increased life-satisfaction.

Nevertheless, this research project entails some methodological challenges. One project challenge is the limited intervention time. A one-week intervention may not be sufficient time to produce significant impact on consumer intent and behavior. However, we chose this short time-period to minimize respondent's time-burden; prolonged intervention periods could increase potential issues in participant commitment and dropout rates.

Additionally, our choice of a control group is limiting. Control groups in intervention studies could be designed in several ways, and they should provide a comparison measurement to that of the intervention. Our findings will be limited in that they do not control for other, non-video interventions, such as written-text or monetary-incentive interventions. By pinging participants daily, and asking them to answer a mood scale, our outlined control condition does control for a placebo effect and a priming effect. Since our research question is inspired by a phenomenon currently occurring in the field (i.e., YouTube Minimalism videos) our control condition allows us to test whether these videos are more beneficial for consumers than having no engagement in a consumption-reduction intervention. Thus, the control condition chosen for this study is not optimal, but it does produce the highest ecological validity. If feasible, both monetarily and logistically, we recommend authors utilizing this protocol include additional control conditions to their design.

Due to the exploratory nature of the study, it is possible, that neither intervention significantly impacts buying intent, behavior, affective state, or life satisfaction. Nevertheless, null results will be highly informative. As evident in the number of Minimalism videos on YouTube, and number of subscribers to this content, it would be expected that this user-generated content is effective in promoting voluntary simplicity. If the outlined study finds that even in controlled settings there is no support for a significant influence of this content on behavior, our results could improve the public's understanding of user-generated content. The results—whether supporting the hypothesis or not—will raise further scientific questions and influence our handling of user-generated content.

In sum, the proposed project aims to contribute to the limited literature on voluntary simplicity and the use of user-generated content in consumer interventions. Specifically, this study might add a literary contribution to consumer values and sustainable behavior, specifically by examining its applicability in promoting voluntary simplicity and reducing excessive consumption through media primed with self-transcendence or self-enhancement messages. Applied implications of the proposed study will be directed to social marketers, social media experts, and proponents of voluntary simplicity.

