## Design

A weeklong intervention program will test the efficacy of watching voluntary simplicity videos in reducing non-essential consumption. The first condition will promote voluntary simplicity while priming self-transcendence values and goals, and the second condition will promote voluntary simplicity while priming self-enhancement values and goals. These two interventions will be compared with a control condition which only measures participant's affective state during the intervention week. All participants will undergo baseline and post-intervention evaluations of values and goals in consumption reduction, voluntary simplicity attitudes and behaviors, spending behaviors, and life satisfaction directly before and directly following the intervention, respectively. A one-month follow up measurement will also be taken. The difference between measurements before and after the intervention will serve as our dependent variables.

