#### Participant criteria

Participants will sign a consent form electronically stating that; (a) they are at least 18 years of age or of legal age in their country of residence, (b) they have not been clinically diagnosed with a disorder related to impulse control or addictions, (c) they express both a desire and difficulty to reduce their non-essential consumption, (d) they have not previously followed the social media trend of consumer Minimalism.

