#### Recruitment methods

Participants will be recruited through convenience sampling via two main avenues; (a) social media posts in consumption related forums and sites as well as Facebook pages and groups, and (b) campus posters circulated around the universities of the research team. The main appeal to participants in all avenues will follow a “question and proposal” format, i.e., “Do you want to decrease your buying? Sign-up to try out an experimental treatment!” Each poster and online recruitment posting will feature a QR code that participants can scan with their smartphones to download the intervention mobile application. The consent form will be embedded in the in-take questionnaire.

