#### Participant commitment through feedback

Efforts to promote continued participation will be aimed at both extrinsic and intrinsic motivation, with a primary emphasis on the latter. Two intrinsic, motivational aspects will be addressed in the recruitment call; (a) participants will be offered to try treatments that may help them with their reported, personal goal of reducing non-essential material consumption and (b) participants will receive feedback on their personal progress following the intervention.

To further motivate participants to remain in the study throughout the weeklong intervention, a lottery prize of 100 euros will be raffled to one participant who completed the full intervention. The winning participant will be able to receive this prize via either bank transfer or a donation made on their behalf to a charity of their choice.

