### Surveys and intervention

After baseline measurement is completed, participants in each intervention group will be requested to watch one video per day for six days, and answer a short questionnaire following each video. The videos will be between three and five minutes long and consist of a young, female presenter, talking to the camera as if talking to an audience.

The main content of the videos in both intervention conditions will be identical. However, the opening and closing sections of each video will be filmed separately, and emphasize either self-transcendence or self-enhancement values and goals, per condition. For example, in the self-transcendence condition the presenter will say, “We are here because we want to *make the world a better place*. By being *environmentally friendly, conscience* and *ethical*, we can *make a positive impact on the world*.” Conversely, in the self-enhancement condition, the presenter will say, “We are here because we want to *make our lives better*. By being *less stressed, more in control*, and *spending wisely*, we can *make a positive impact on our own lives*.” Moreover, visual stimuli integrated into the videos will prime participants of either self-transcendence, biospheric values (e.g., gardens, lakes, plants) or self-enhancement, hedonic and egoistic values (e.g., friends chatting and drinking coffee together). In the control condition, there will be no intervention, but participants will be pinged by the mobile application to answer a survey once per day for six days. Follow-up measurements will be conducted via web-site one month after the last intervention day for all three groups.

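### The daily mood-survey control matches app contact and repeated measurement, not expectation of benefit, so the protocol's claim that it controls for placebo should be removed

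*Protocol article*

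**What the plan says.** The claim stands in Anticipated results, in the paragraph on the choice of control group: by pinging participants daily and giving them a mood scale, "our outlined control condition does control for a placebo effect and a priming effect".

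Other sections describe what the arms receive and what participants were offered:

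- **Control arm.** Design calls it "a control condition which only measures participant's affective state during the intervention week". Surveys and intervention says "In the control condition, there will be no intervention, but participants will be pinged by the mobile application to answer a survey once per day"; this lasts six days.
- **Video arms.** Under Surveys and intervention, "participants in each intervention group will be requested to watch one video per day for six days, and answer a short questionnaire following each video".
- **Recruitment, all arms.** The advertised appeal in Recruitment methods is "Sign-up to try out an experimental treatment". Participant commitment through feedback adds that "participants will be offered to try treatments that may help them with their reported, personal goal of reducing non-essential material consumption".
- **Who is enrolled.** Under Participant criteria, consenting participants state that "they express both a desire and difficulty to reduce their non-essential consumption".

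The same paragraph of Anticipated results calls the control group limiting and not optimal. The limitation it names is that other kinds of intervention, such as written text or monetary incentives, are not compared. It also says that the control lets the study compare the videos with having no consumption-reduction intervention at all.

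**The concern.** To control for placebo, a comparator must create a similar expectation of benefit without the active ingredient. This control is a measurement-only arm in people who volunteered because they want help with a goal. The video arms receive a daily programme openly directed at that goal; the control arm receives a daily question about mood.

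At stake is the reading of the first research question in Objectives, whether user-generated content reduces excessive consumption. If the placebo claim is believed, a difference between videos and control will be read as the effect of the content with non-specific influences already removed. The design does not have that property. The article also addresses other authors who may use the protocol, so the claim could be copied along with the control condition.

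**Working it through.** **No stated figure decides this point.** It turns on what the control condition shares with the video conditions. Setting the sections side by side:

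| Feature | Video arms | Control arm | Matched? |
|---|---|---|---|
| Recruitment appeal, app, promised progress report | Yes | Yes | Yes |
| Baseline and post-intervention consumption questionnaires | Yes | Yes | Yes |
| One push notification and short survey a day | Yes | Yes | Yes |
| Receives something presented as help with the goal | Yes | No | No |
| Daily attention to reducing consumption | Yes | No (mood only) | No |
| Reason to feel that less buying should be reported after a programme | Yes | Less | No |

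The matched rows are contact and repeated measurement, and the influences they carry cancel in the comparison. The unmatched rows are what a placebo control is meant to equalise. The outcomes under Measures (shopping intention, shopping frequency, weekly non-essential expenditure, life satisfaction) are self-reported and so open to these influences. Adjusting for intake motivation, as Proposed analysis plans, does not help: it is an intake measure and cannot carry an expectation difference created by receiving or not receiving a programme.

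The self-transcendence and self-enhancement arms match on every row. They share the main video content and differ in the opening and closing sections and the visual priming.

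**Illustration of size**

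Inputs from Sample size: N = 198 before the dropout allowance, alpha .05 (taken as two-sided). As a check on that N, the within-between interaction formula with f = .10, 3 groups, 3 measurements, and an assumed correlation of .5 and sphericity gives power 0.792 at 198, against the stated .80. The article does not give the number of measurements or the correlation. The match has no bearing on the point; 198 is used only to set the precision.

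Assumptions, not in the article: equal allocation (198/3 = 66 per arm, so 132 video and 66 control), baseline-adjusted analysis, baseline-to-outcome correlation rho between 0.3 and 0.7, no content effect, and a non-specific effect of d SD.

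SE = sqrt[(1 − rho²)(1/132 + 1/66)], where 1/132 + 1/66 = 0.02273.

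P(p<.05) = Φ(d/SE − 1.96) + Φ(−d/SE − 1.96).

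| rho | 1 − rho² | SE | d = 0.1 | d = 0.2 | d = 0.3 |
|---|---|---|---|---|---|
| 0.3 | 0.91 | 0.1438 | 11% | 29% | 55% |
| 0.5 | 0.75 | 0.1306 | 12% | 34% | 63% |
| 0.6 | 0.64 | 0.1206 | 13% | 38% | 70% |
| 0.7 | 0.51 | 0.1077 | 15% | 46% | 80% |

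For example, at rho = 0.5 and d = 0.3, 0.3/0.1306 = 2.298, and Φ(2.298 − 1.96) = Φ(0.338) = 0.63. With d = 0 the rate is the nominal 5%.

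**The case against.** The strongest reply is that the article already states the comparison correctly. The sentence after the placebo claim presents the contrast as videos against no consumption-reduction intervention, the paragraph justifies this by ecological validity, and it recommends further control conditions to others. A no-treatment comparator is a legitimate choice. The claim sits in a discussion of limitations and changes no endpoint, model, allocation or sample size. The control also does real work: Proposed analysis expects consumption to fall in every arm, and change due to enrolment and repeated measurement cancels. All of this stands. It narrows the point to a specific false statement and its consequence for wording. It does not rescue the statement, because the limitation conceded concerns other intervention formats, whereas on placebo the article asserts control.

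Three stronger readings are tempting and are not supported:

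- **That a video-control difference cannot be credited to the content.** Content is part of the randomised package, and the package effect is estimated validly. What is lost is the separation of content from expectation and demand.
- **That controls can tell they were given no treatment, or that the trial is unblinded.** The article does not say what controls are told about their allocation. It shows only that they receive nothing directed at the goal for which they signed up.
- **That the statement on effectiveness under Ethics process also needs correcting.** It refers to comparison with the control condition and makes no placebo claim.

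**Conclusion.** The placebo claim in Anticipated results is wrong as written. The control matches app contact and repeated measurement; it does not match expectation of benefit, daily attention to the goal, or demand. The randomised estimate of video programme versus daily mood pings remains valid, and the comparison between the two video arms is unaffected.

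The conclusion rests on the article's own description of the arms and of recruitment. The percentages do not support it and are not needed for it. They show only that a modest non-specific effect, if there were one, could often produce a significant result with no content effect. The effect size, the correlation and equal allocation are all assumed, and nothing in the article shows that an effect of 0.3 SD exists.

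**What to change.** - In Anticipated results, delete the claim of placebo control. Say that the daily survey matches contact and repeated measurement only.
- In the same paragraph, list expectation of benefit and demand as uncontrolled, beside the limitation already given.
- Word the conclusion on the first research question (Objectives and Anticipated results) as the effect of the video programme compared with daily mood pings and no consumption-reduction intervention.

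This costs a few sentences and a narrower headline claim. No arm, sample size or schedule changes.

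Optionally, an item on expected benefit could be asked in all three arms. It would describe a difference in expectation, not remove it. It would not capture demand, would be affected by exposure if asked after the first video, and might itself prompt expectation or awareness in controls. The wording change is the essential part.

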## Ethics statement

This study has received ethical approval from the Cambridge Psychology Research Ethics Committee.
